### Data Monitoring, Harms, and Auditing

2.15

Given the low‐risk nature of this nutritional intervention trial, no formal data monitoring committee will be established. Interim analyzes will not be conducted, as the study duration is short. Potential adverse events (e.g., gastrointestinal discomfort, beeturia) will be monitored via participant self‐reports during visits and follow‐up calls. Serious adverse events, though unlikely, will be reported immediately to the ethics committee and documented in trial records. Independent audits of trial conduct will be performed by the university's research office at midpoint and completion to ensure protocol adherence.

### Study Assessments

2.16

Participants will undergo initial and concluding evaluations encompassing several assessments. These will include a comprehensive questionnaire gathering general information, the International Physical Activity Questionnaire, a 72‐h food recall prior to testing, and administration of the Rate of Perceived Exertion (RPE) Scale during upper and lower body Wingate tests using the Borg scale [39]. Additionally, participants will receive a detailed list of foods rich in nitrates and will be instructed to abstain from consuming these items throughout the study duration.

### Data Collection Methods

2.17

Data will be collected using standardized forms and electronic records. Wingate test data will be recorded directly from the Monark ergometer software. Blood samples will be analyzed in a certified laboratory using automated analyzers for CK, LDH, and glucose. RPE will be assessed via the Borg scale immediately post‐test. A 72‐h food recall will be administered by trained staff to verify dietary adherence. All data will be double‐entered to minimize errors.

### Anthropometric Measurements

2.18

Height will be measured on a flat surface without shoes using a stadiometer. Weight, fat mass (FM), and fat‐free mass (FFM) will be assessed using a bioelectrical impedance analyzer (InBody 720 Body Composition Analyzer).

### Device Base Parameters

2.19

To evaluate upper body Wingate test indices, a Monark cycle ergometer (Ergomedic 891E, Vansbro, Sweden) will be used, and to evaluate lower body Wingate test indices, a Monark cycle ergometer (Ergomedic 891E, Vansbro, Sweden) will be utilized. The load (kgf) will be set at 7.5% of each participant's body weight for the lower body Wingate test and 5% of body weight for the upper body Wingate test [40].

### Laboratory Analysis

2.20

To assess serum levels of certain parameters, 10 mL venous blood samples will be collected at each blood draw, and the levels of lactate dehydrogenase, creatine kinase, and blood sugar will be measured.

### Statistical Analysis

2.21

Data will be analyzed using SPSS v26. Normality will be assessed via the Shapiro‐Wilk test. Comparison of the within‐subject effects of BRJ (90 mg vitamin C) versus placebo will be evaluated using paired t‐tests (for normal data) or Wilcoxon signed‐rank tests (for non‐normal data). A univariate General Linear Model (GLM) will be used to assess treatment, sequence, and treatment‐sequence (carryover) effects. Statistical significance will be set at *p* < 0.05.

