### Power Calculation and Sample Size Estimate

2.8

Sample size was calculated based on mean power data from a previous study by Williams et al. (2020) [37] (placebo: 508.14 ± 117.55 W; BRJ: 607.36 ± 112.28 W). The required sample size was calculated to be 22 participants for a crossover design considering 95% confidence and 80% power using the following equation:

$$n=\frac{(k\times \delta_{1}^{2}+\delta_{2}^{2}){\left(Z_{1-\alpha /2}+Z_{1-\beta }\right)}^{2}}{{∆}^{2}}.$$

In the above equation, n is the sample size in each group, k is the ratio of the groups (which is 1 in this study), δ is the standard deviation in each group, Δ is the difference of group means, Z_{1‐α/2} is considered 1.96 for a 95% confidence interval, and Z_{1‐β} is the power of the study. To account for potential participant dropout and ensure completion of all study sessions, 28 participants were recruited.

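### The beetroot-placebo comparison has no period term, and the model that could supply one labels the period effect as carryover

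*Protocol article*

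**What the plan says.** Section 2.21 (Statistical Analysis) begins with a check: "Normality will be assessed via the Shapiro‐Wilk test". The within-person comparison of beetroot juice with placebo is then "evaluated using paired t‐tests (for normal data) or Wilcoxon signed‐rank tests (for non‐normal data". The text does not say whether normality is judged on the paired differences or on the raw values. A univariate general linear model follows, which "will be used to assess treatment, sequence, and treatment‐sequence (carryover) effects". Period or visit is not named as a factor, no participant term is named, and the paired test and the model are not ranked.

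The design around it: sections 2.3 and 2.5 describe two laboratory visits separated by a 14-day washout, with no familiarisation session described. Section 2.13.1 allocates the two sequences 1:1. Section 2.8 states "The required sample size was calculated to be 22 participants for a crossover design" and adds "To account for potential participant dropout and ensure completion of all study sessions, 28 participants were recruited". The allowance is therefore 28 − 22 = 6 losses.

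**The concern.** A two-period crossover confounds treatment with visit inside each person. The analysis removes this by comparing the two sequences, which see the treatments in opposite order. A paired test on pooled differences does not do so. Any general shift between visit 1 and visit 2 (practice, conditioning, season) is subtracted from the beetroot effect in those who take beetroot first and added to it in those who take placebo first. When the sequences are equal in size the shifts cancel in the mean but remain in the variance. When they are unequal, part of the shift stays in the estimate.

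The model in the same section ought to be the remedy, but its terms are misnamed. A plain practice effect would appear as a significant carryover, which would cast doubt on the washout for no reason, while the paired comparison stayed unadjusted.

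**Working it through.** **Inputs.** From section 2.8: "placebo: 508.14 ± 117.55 W; BRJ: 607.36 ± 112.28 W", difference 607.36 − 508.14 = 99.22 W; two-sided 5% level, since the normal quantile "is considered 1.96 for a 95% confidence interval"; 80% power; 22 required and 28 taken. From section 2.13.1: 14/14 at randomisation. The documents give neither a period effect nor a within-person correlation. Both are assumed below: SD 115 W per visit, correlation ρ from 0.5 to 0.9, period effect π from 15 to 50 W.

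**The plan's own figure.** n = (117.55² + 112.28²) × (1.96 + 0.8416)² / 99.22² = 21.07, rounded up to 22. It reproduces. The formula has no correlation term, so it says nothing about ρ.

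**How period enters.** Let τ be the treatment effect and π the gain at visit 2. The expected beetroot-minus-placebo difference is τ − π in beetroot-first participants (n_BP) and τ + π in placebo-first participants (n_PB). With N = n_BP + n_PB:

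- Bias of the paired mean = π(n_PB − n_BP)/N.
- Expected variance of the pooled differences = s² + (4·n_BP·n_PB/N²)·π²·N/(N − 1), where s² = 2(1 − ρ)·SD².

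**Balanced, 14/14, ρ = 0.8.** s = 115 × √0.4 = 72.7 W, so the standard error is 72.7/√28 = 13.7 W. With π = 50 W the variance is 72.7² + 50² × 28/27, the SD is 88.8 W and the paired standard error is 16.8 W. By simulation, for τ = 50 W:

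| π | Paired t-test | Period-adjusted |
|---|---|---|
| 25 W | 92% | 94% |
| 50 W | about 87% | 94% |

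At the planning difference of 99.22 W with π = 50 W, the worst case over ρ = 0.5 to 0.9 is 0.987 versus 0.993 at 14/14 and 0.954 versus 0.969 at 11/11. The paired test is conservative under balance: at ρ = 0.8 and 14/14 its type I error is 0.034 for π = 30 W and 0.017 for π = 50 W, against about 0.05 with period adjustment.

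**Unequal completers.**

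- 10 beetroot-first, 12 placebo-first: (12 − 10)/22 = 0.09, so 0.09π, or 4.5 W for π = 50 W.
- 8 and 14 (all six losses in one sequence): (14 − 8)/22 = 0.27, so 4.1, 8.2 and 13.6 W for π = 15, 30 and 50 W. Type I error of the paired test lies between 0.051 and 0.069.
- With period in the model the bias is 0 in every case.

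**The treatment-by-sequence term.** Code beetroot +1 and placebo −1; beetroot-first +1 and placebo-first −1; visit 1 as +1 and visit 2 as −1.

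| Cell | Treatment | Sequence | Product | Period |
|---|---|---|---|---|
| Beetroot-first, visit 1 | +1 | +1 | +1 | +1 |
| Beetroot-first, visit 2 | −1 | +1 | −1 | −1 |
| Placebo-first, visit 1 | −1 | −1 | +1 | +1 |
| Placebo-first, visit 2 | +1 | −1 | −1 | −1 |

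The product column equals the period column. Carryover in this design is aliased with the sequence main effect, not with this term.

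**Shapiro-Wilk selection, n = 22.** Type I error of the two-stage procedure is 0.053 for normal differences and 0.048 for t(3) differences. For strongly skewed differences with mean zero (centred exponential) it is 0.126, against 0.076 for the t-test alone, because the signed-rank test then addresses a different hypothesis.

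**The case against.** The best defence is that period is already in the plan under another name. The general linear model contains the period column, so its treatment effect is adjusted for period. This stands as algebra, and it means that the plan as a whole does not ignore period. It does not settle the matter, because the explicit beetroot-placebo comparison is given to the paired test and the term is labelled carryover. A participant factor may simply be left out of a condensed description. If it were absent from the model, the treatment contrast would carry between-person variance: 115 × √(2/28) = 30.7 W at 14/14, against 13.7 W within person at ρ = 0.8.

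Second, a reader might infer that the paired test inflates the false-positive rate. It does not under balance, where the rate falls below 5%. Even at 8/14 it reaches only about 7% in the scenarios examined. What grows is the error variance.

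Third, a reader might take the 8/14 bias as expected. If six of 28 leave regardless of sequence, all six fall in one sequence with probability about 1.6%. The split is 11/11, 12/10 or 10/12 in about 84% of cases, and the mean absolute bias is about 0.075π (3.8 W for 50 W). A larger bias needs dropout that depends on sequence.

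Fourth, no passage shows that a period effect exists, and 50 W is half the planning difference. This also stands, and it is why the sizes are given as a range.

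Finally, the normality switch costs little unless the differences are markedly skewed.

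**Conclusion.** The point holds as a correctable weakness in the stated analysis. The test assigned to the treatment comparison has no period term, and the model that contains one attributes it to carryover. Under balance the consequence is lost precision. At SD 115 W, ρ = 0.8 and 14/14, the loss for a 50 W effect is about 2 percentage points of power with a 25 W period effect and about 7 with 50 W, and it is negligible if the true effect is as large as planned. Bias needs both a period effect and unequal completers, and is small at the splits most likely to occur. These sizes rest on an assumed correlation and an assumed period effect. The mislabelling rests on no assumption: it follows from the design.

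**What to change.** Name one primary analysis: a mixed model with treatment, period and sequence as fixed effects and participant as a random effect, or the equivalent two-sample comparison of period differences between the sequences. Rename the treatment-by-sequence term as period, and state that carryover cannot be separated from the sequence effect in this design. Replace the Shapiro-Wilk switch with this one model, and keep a rank-based analysis as sensitivity only.

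The cost is a few sentences and one degree of freedom. If there is no period effect, the power lost with balanced sequences is too small to matter. At 8/14, power for a 40 W effect at ρ = 0.8 would be 0.66 instead of 0.69. Section 2.1 says that recruitment had not begun at version 1.0, so if that is still so the change can be made before any data exist.

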### Participant Timeline

2.3

Participants will attend two laboratory visits, separated by a 14‐day washout period. Each visit will follow this schedule:
T = 0 h: Arrival, confirmation of adherence to pre‐test instructions, supplement administration (beetroot or placebo).T = 3 h: Baseline blood sample collection, anthropometric measurements.T = 3+ hours: Upper body Wingate test, followed by lower body Wingate test (1–4 min later), with RPE assessment during tests.Immediate post‐test: Blood sample collection.T = 27 h (24 h post‐test): Follow‐up blood sample (Figure 3).

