### Control Group

2.5

Participants assigned to the control group will receive a beverage that visually resembles the beetroot supplement. The placebo drink will consist of a neutral solution containing 0.4 mg/mL citric acid, 0.2 mg/mL food coloring, and 0.25 g/mL sugar, formulated to match the appearance, taste, and texture of the beetroot juice without containing nitrates, vitamin C, or polyphenols.

The beetroot juice intervention will be similarly supplemented with 0.25 g/mL sugar to ensure identical sweetness and caloric content, maintaining effective blinding. Both drinks (240 mL each) will be prepared by a third‐party supplier to ensure consistency and double‐blinding.

After a 3‐h interval, a baseline blood sample will be collected from the subjects. The Wingate upper body functional test will be performed immediately thereafter, followed by the Wingate lower body test, which will be conducted 1 to 4 min later. Blood samples will be collected immediately after the Wingate lower body test and again 24 h later. Additionally, participants will complete the RPE questionnaire during both test sessions.

Given that the half‐life of nitrate is approximately 5 to 8 h, a 14‐day washout period is considered sufficient to effectively reduce any residual effects that may arise from prior nitrate supplementation [35]. Since participants will serve as their own controls, sessions will be scheduled at the same time each day to maintain consistency.

The study's design is illustrated in Figure 3. Throughout the experimental phase, each participant will complete two visits to the laboratory.

Studies have also demonstrated that the performance of high‐intensity lower body exercises is not significantly compromised by prior upper body activity. As such, it will be feasible to conduct lower body testing and training either preceding or following upper body sessions without negatively affecting the power output of the lower body [36]. In this study, we will administer the upper body Wingate test, followed by the lower body Wingate test. This sequential testing design will enable a thorough assessment of the effects of the two supplements on performance across different muscle groups.

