### Allocation: Sequence Generation, Concealment, and Implementation

2.13

This double‐blind, placebo‐controlled, crossover study will randomize 28 semi‐professional wrestlers to receive either beetroot juice enriched with 90 mg vitamin C (8.4 mmol nitrate) or a placebo drink (240 mL each) in random order, with a 14‐day washout period to eliminate carryover effects. Randomization will be performed using a web‐based tool, with allocation details concealed in consecutively numbered opaque envelopes managed by an independent staff member.

Blinding will be maintained for participants, assessors (care providers), and investigators. The intervention and placebo drinks will be visually identical. Drinks will be prepared and labeled with participant numbers by the independent staff member, ensuring that participants and assessors (conducting Wingate tests, blood sampling, and RPE questionnaires) remain unaware of group allocations. Investigators overseeing the study will have no access to allocation details until data collection is completed. Data will be coded with participant numbers to maintain unbiased analysis.

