#### Sequence Generation

2.13.1

Randomization will be performed using a web‐based tool to generate a balanced crossover sequence (1:1 allocation to start with beetroot or placebo).

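### The GLM's treatment-by-sequence term is labelled carryover, but in this two-period crossover it is the period effect; differential carryover lies in the sequence term

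*Protocol article*

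**What the plan says.** The design is a two-sequence, two-period crossover. Participant Timeline (2.3) says: "Participants will attend two laboratory visits, separated by a 14‐day washout period". Sequence Generation (2.13.1) describes a "balanced crossover sequence (1:1 allocation to start with beetroot or placebo"), which gives 14 wrestlers per sequence if all 28 are randomised evenly.

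Statistical Analysis (2.21) gives two analyses. The within-subject comparison of beetroot with placebo "will be evaluated using paired t‐tests (for normal data) or Wilcoxon signed‐rank tests (for non‐normal data"). Then: "A univariate General Linear Model (GLM) will be used to assess treatment, sequence, and treatment‐sequence (carryover) effects". The threshold is p < 0.05. Period is not named as a factor anywhere.

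On carryover itself, the article relies on design. Allocation (2.13) describes the drinks as given "with a 14‐day washout period to eliminate carryover effects", and Control Group (2.5) says that "a 14‐day washout period is considered sufficient to effectively reduce any residual effects", citing a nitrate half-life of about 5 to 8 h.

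**The concern.** The sentence assigns a meaning to a model term, and the assignment is wrong for this design. With two periods and two sequences, knowing a wrestler's sequence and current drink tells you which visit it is. The treatment-by-sequence interaction is therefore the visit effect under another name.

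Two wrong readings follow. A gain from visit 1 to visit 2 on maximal sprint tests, with no carryover at all, would be reported as carryover and would cast doubt on a sound result and on the washout. Conversely, if the two drinks carried over in opposite directions, the labelled term would show nothing while the treatment estimate was biased.

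**Working it through.** **Inputs.** Two visits (2.3, 2.5), two sequences at 1:1 (2.13.1), 28 wrestlers and alpha 0.05 (2.21). The SDs are in 2.8: 117.55 W and 112.28 W. They reproduce the protocol's sample size, which is not in dispute: (117.55² + 112.28²)(1.96 + 0.8416)² / 99.22² = 21.07, rounded up to 22. Their pooled value is √[(117.55² + 112.28²)/2] = 114.95, taken as 115 W. These SDs are for mean power; none is given for maximum power, the primary outcome. The within-wrestler correlation ρ and the period effect are not given. I assume ρ from 0.5 to 0.9 and visit-2 gains of 25 W and 50 W.

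**Algebra.** Let τ be the treatment effect, p1 and p2 the period effects, and λB and λP the carryover from beetroot and placebo into visit 2. Expected values:

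| Sequence | Visit 1 | Visit 2 |
|---|---|---|
| Beetroot first | τ + p1 | p2 + λB |
| Placebo first | p1 | τ + p2 + λP |

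- Treatment by sequence = (τ + p1 − p2 − λB) − (τ + p2 + λP − p1) = 2(p1 − p2) − (λB + λP).
- Sequence (difference of sums) = (τ + p1 + p2 + λB) − (p1 + τ + p2 + λP) = λB − λP.
- Treatment (mean of the two differences) = τ − (λB − λP)/2.

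The interaction thus holds period and average carryover, inseparably. The difference λB − λP, which biases treatment, appears only in sequence.

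**Numerical check** (effect-coded coefficients, τ = 0):

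| Truth | Treatment | Sequence | Treatment × sequence |
|---|---|---|---|
| Period gain 40 W, no carryover | 0 | 0 | −20 |
| Beetroot carryover 40 W only | −10 | +10 | −10 |
| Beetroot +40 W, placebo −40 W | −20 | +20 | 0 |
| Both +40 W | 0 | 0 | −20 |

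The first and last rows are identical, so a period gain cannot be told from common carryover. In the third row the treatment difference is biased by 2 × (−20) = −40 W while the labelled term is zero. Adding a period column to the listed model leaves its rank at 4, so period is already there under the other name.

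**False carryover rate, participant in the model.** The contrast is 2 × gain, with standard error √[2 × 115² × (1 − ρ) × 2/14]: 43.5, 27.5 and 19.4 W at ρ = 0.5, 0.8 and 0.9. For a 50 W gain the ratios are 100/43.5 = 2.30, 100/27.5 = 3.64 and 100/19.4 = 5.14. On a noncentral t with 26 degrees of freedom the term is significant in about 60%, 94% and over 99% of trials. For 25 W the rates are about 20%, 42% and 70%.

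**False carryover rate, only the listed terms fitted.** By simulation (error about 1 percentage point), a 50 W gain is flagged in about 31%, 25% and 20% of trials, and at ρ = 0.8 a 25 W gain in about 1%. The sequence test is too liberal here, because its true variance is (1 + ρ) times the one assumed. Its large-sample size is 2[1 − Φ(1.96/√(1 + ρ))] = 11%, 14% and 16%, and simulation gives 10% to 16%.

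**Paired test.** Under 14:14 balance the period effect cancels from the mean difference but stays in its variance. At ρ = 0.8, power for a 50 W treatment effect falls from about 94% with no period effect to about 86% to 87% with a 50 W period effect. A period-adjusted analysis keeps about 94%. If dropout broke the balance, say 13:9 among 22 completers, a 50 W period effect would shift the paired estimate by (4/22) × 50 = 9 W.

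**The case against.** The algebra cannot be disputed, but several larger readings can, and the documents do not support them.

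- *The model has no period adjustment.* A reader might infer this because period is not named. The interaction is period, so the fault is the label and its interpretation.
- *The term has nothing to do with carryover.* It contains average carryover. It is non-specific, not unrelated.
- *The crossover's precision is lost.* With only the listed terms, the GLM treatment test at ρ = 0.8 has a standard error 1/√0.2 = 2.2 times the within-wrestler one, and power for 50 W falls from 94% to 24%. But 2.21 lists effects to be assessed, in a condensed article, and the named software's univariate GLM accepts participant as a random factor. The within-subject comparison is also assigned to the paired test, which does not suffer this loss.
- *All the bad figures apply at once.* They do not. The 60% to over 99% flagging rates need participant in the model; the liberal sequence test and the power loss need it absent.
- *A carryover finding would overturn the result.* No rule in the article makes a significant carryover term change or discard an analysis.
- *There was certainly no familiarisation.* The article describes none, but it is condensed, and Consent Process (2.11) mentions an initial screening visit. A practice effect is plausible, not shown.

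What stands of the objection is that this is a supplementary model and the treatment conclusion rests mainly on the paired test. What it does not remove is that the article itself attaches the carryover label.

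**Conclusion.** The point holds as a mislabelled and misread term in a supplementary model, to be rated should-fix. The aliasing is exact and needs no assumption beyond two sequences and two periods. How often it would mislead depends on figures the documents do not give. Under the assumptions above, a 50 W visit-2 gain with no carryover is called carryover in about 60% to over 99% of trials with participant in the model, and in about 20% to 31% without. The same label misses opposite carryover at any sample size. The effect on the paired treatment test is limited: no bias under 1:1 balance, and some loss of power if a period effect exists.

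**What to change.** Replace the GLM sentence in 2.21 with: a linear mixed model with treatment, period and sequence as fixed effects and participant within sequence as a random effect; the treatment estimate and its 95% CI come from this model. Period takes the place of the treatment-by-sequence term; adding it beside that term would be redundant. If the paired test is kept, state that it is supportive.

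Delete the carryover label. State that carryover is excluded by design, on the article's own ground of a 14-day washout against a 5 to 8 h half-life (336 h, or 42 to 67 half-lives). Report the sequence effect, tested against between-participant error, as descriptive only and not as a trigger for a different analysis.

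The cost is the wording of one paragraph. The model runs in the named software, needs no new data or visits, and leaves the sample size unchanged. Version 1.0 states that recruitment had not begun.
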